
### Aims and hypotheses

The aims of the present EPO trial are threefold. First, we aim to investigate whether 12 weekly recombinant human EPO infusions ameliorate cognitive impairments in first-degree relatives without psychotic or mood disorders to patients with BD, recurrent UD, or schizophrenia (sub-study 1). This will allow for the first time to judge the disease-independent response of inherent cognitive genetic traits. Second, we will examine whether a longer treatment period is associated with similar or stronger cognitive improvement in remitted patients with BD or recurrent UD (defined as ≥ 2 treatment-requiring depressive episodes) (sub-study 2). Third, we will explore with fMRI the early neuronal changes that are predictive of subsequent clinically relevant cognitive improvement across these groups. We hypothesize that:12 weekly EPO infusions improve cognition in first-degree relatives and remitted patients with BD or recurrent UD in comparison with saline.EPO versus saline-treated participants will display early cognition-related neural activity in dorsal PFC in the direction of the activity in healthy controls, which will correlate with cognitive improvement.

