The baseline assessment is divided into two days, 1–3 days apart for practical reasons and to avoid attrition. On the first day of the baseline assessment, participants are mood rated with the HDRS-17 and YMRS to ensure remission and afterwards complete an fMRI scan at Copenhagen University Hospital, Rigshospitalet. On the second baseline day, participants attend Psychiatric Centre Copenhagen for a fasting research blood test (peripheral biomarker measure) followed by an assessment of cognitive functions with a neuropsychological test battery, verbal IQ (assessed with the Danish Adult Reading Test; DART [56]), and filling in questionnaires concerning subjective cognitive complaints, quality of life, level of functioning, and functional capacity, as well as depression and mania symptom severity ratings. Functional capacity will be assessed using a clinician-rated interview and a performance-based task. Mood ratings are performed with the HDRS-17 [51] and the YMRS [52]. After two weeks of treatment (i.e. two doses of EPO or saline), fMRI scan, research blood samples, neuropsychological testing, mood ratings, and questionnaires on subjective cognitive difficulties are repeated. After treatment completion (week 13) and at the six-month follow-up, the neuropsychological tests, questionnaires concerning subjective cognitive complaints, quality of life, and functional capacity (self-reported and performance-based) are repeated. Research blood samples are collected in week 13, but not at the six-month follow-up. Sleep quantity and quality in the past three days is assessed before each of the four major assessment time points and with online self-rating using the Pittsburgh Sleep Quality Inventory (PSQI) [60] assessing sleep quality one week before the baseline, week 3, week 13, and the six-month follow-up assessment. Blood samples are collected at baseline and weeks 3 and 13 for assessment of potential blood-based biomarkers of pro-cognitive effects. An intermediate mood symptom rating for patients (sub-study 2) is performed at week 7 to assess whether they are in (partial) remission throughout the study period. To ensure safety, we conduct weekly monitoring, comprising thorough medical examinations and blood test evaluations, for the duration of the treatment course and in weeks 13 and 15. Pregnancy tests are mandatory for and will be performed on fertile female participants before the first study medication infusions and every second week during the active treatment period. Blood screening and thorough medical examinations are undertaken at baseline, weekly throughout the 12-week treatment period as well as one and three weeks after treatment completion to continuously monitor red blood cell levels and ensure participant safety.

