#### Functional MRI analyses

Functional MRI data are pre-processed and analyzed with FMRIB Expert Analysis Tool (FEAT) and the “randomize” algorithm implemented in FSL (FMRIB Software Library; www.fmrib.ox.ac.uk/fsl). We will assess whether early differences between EPO and placebo groups in task-related neural activity during each of the three fMRI paradigms after two weeks of treatment (adjusted for baseline activity) predict subsequent treatment efficacy on cognition at treatment completion. Neuropsychological test performance and fMRI data from 40 cognitively intact healthy controls without personal or first-degree relative history of mental illness from the BIO study [85] is used as external normative data.

Region of interest (ROI) analyses of fMRI data from the N-back working memory tasks will be carried out to investigate the effects of EPO on neural activity in dlPFC. The difference in neural activity between the EPO and saline groups in week 3 will be investigated by extracting and analyzing mean percent signal change in dlPFC adjusted for potential differences in baseline activity using univariate analysis of covariance (ANCOVA) and with whole-brain analyses (FEAT) in week 3 (with adjustment for potential activity differences at baseline). We will also investigate the hypothesized early dorsal PFC activity change in response to EPO versus saline with volume of interest (VOI) for the dorsal PFC. Volume of interest analyses of dorsal PFC and the hippocampus are conducted to assess fMRI data from the Strategic Picture Encoding Task. Finally, exploratory whole-brain analyses are conducted to assess treatment-related activity change in other brain regions. Differences in neural activity between groups will be correlated with potential change in the primary cognitive composite score at week 3 and after treatment completion. If this correlation is significant, multiple regression analyses will be performed with adjustment for mood symptoms, age, and gender to assess the potential predictive value of early neural activity change for potential pro-cognitive efficacy after 12 weeks of EPO treatment.

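### The planned week-13 regression cannot tell neural change that predicts later cognitive improvement from neural change that only tracks cognition at the week-3 scan visit

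*Protocol article*

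**What the plan says.** Under Aims and hypotheses, the third aim is to explore with fMRI the "early neuronal changes that are predictive of subsequent clinically relevant cognitive improvement". The Functional MRI analyses section repeats the idea: differences between the arms after two weeks are examined to see whether they "predict subsequent treatment efficacy on cognition at treatment completion".

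Study design and procedures shows that the scan is not the only measurement at that visit. After two doses, "fMRI scan, research blood samples, neuropsychological testing, mood ratings, and questionnaires on subjective cognitive difficulties are repeated".

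The analysis has two steps. First, differences in neural activity "will be correlated with potential change in the primary cognitive composite score at week 3 and after treatment completion". Second, if the correlation is significant, "multiple regression analyses will be performed with adjustment for mood symptoms, age, and gender". The stated purpose of the second step is "to assess the potential predictive value of early neural activity change for potential pro-cognitive efficacy after 12 weeks of EPO treatment". The composite at week 3 is not among the named covariates. The sample size section measures the clinically relevant difference as change from baseline to week 13.

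**The concern.** The outcome interval overlaps the marker interval. Change from baseline to week 13 is the sum of two parts: change from baseline to week 3, which coincides with the neural change, and change from week 3 to week 13, which comes after it. Only the second part is subsequent to the scan. A correlation with the total can come entirely from the first part.

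Mood symptoms, age and gender do not separate the two parts. The separate week-3 correlation examines the concurrent link but does not remove it from the week-13 result. The problem is one of timing and would remain within a single treatment arm.

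At stake is the interpretation of the biomarker finding. A scan that carries the same information as the cognitive tests given at that assessment may still be of mechanistic interest. It would not show that neural change anticipates later gains, or that it adds to the week-3 test score.

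**Working it through.** **The plan's own figure.** The only calculation in the article is for the primary outcome: difference 0.4, SD 0.5, two-sided alpha 5%, power at least 80%.

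- Per arm: 2 × (1.960 + 0.842)² × (0.5/0.4)² = 24.5, so 25. The plan uses 26.
- Power with 26 per arm: 82.2% (normal approximation) or 80.7% (noncentral t, 50 df).
- Drop-out: 52/0.90 = 57.8, so 58.

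These figures reproduce and are not in dispute. They supply n = 52 per sub-study, or 104 if the sub-studies are pooled. No calculation is given for the fMRI prediction analysis.

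**Set-up.** Let M be the neural change, D3 the composite change from baseline to week 3, and D13 the change from baseline to week 13. Take a marker linked to D13 only through D3:

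- corr(M, D3) = r1
- corr(D3, D13) = r2
- no link between M and D13 once D3 is known, so corr(M, D13) = r1 × r2

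The documents give neither r1 nor r2. Both are assumptions, varied below. An r2 near 0.5 is a natural starting point, because both changes subtract the same baseline. With equal variances σ² and equal between-visit correlation ρ, cov(D3, D13) = ρσ² − ρσ² − ρσ² + σ² = σ²(1 − ρ), and each variance is 2σ²(1 − ρ). The ratio is 0.5 whatever ρ is, with no treatment effect at all.

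**Simulation.** There were 4,000 trials per setting. The planned sequence is a correlation of M with D13 at p < 0.05, then a regression of D13 on M with mood, age and gender (simulated as unrelated to cognition), again at p < 0.05. The last column is the regression with D3 added.

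| r1 | r2 | r1 × r2 | Planned sequence, n = 52 | Planned sequence, n = 104 | With D3 added |
|---|---|---|---|---|---|
| 0.3 | 0.5 | 0.15 | 16% | 30% | about 5% |
| 0.3 | 0.6 | 0.18 | 21% | 43% | about 5% |
| 0.5 | 0.6 | 0.30 | 56% | 86% | about 5% |
| 0.5 | 0.7 | 0.35 | 69% | 95% | about 5% |
| 0.5 | 0.8 | 0.40 | 81% | 99% | about 5% |

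As a reference, r1 = 0 gives about 4% under the planned sequence.

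**Hand check of the correlation step.** The probability is about Φ(atanh(r) × √(n − 3) − 1.96). For r = 0.30 and n = 52: 0.3095 × 7 = 2.167, and Φ(0.207) = 58%; the simulation gave 61% for this step alone. For r = 0.40: 0.4236 × 7 = 2.966, and Φ(1.006) = 84%; the simulation gave 85%.

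**Fewer scans.** The Participants section keeps people with claustrophobia or metal implants in the trial but out of the scanner, so n for this analysis may be below 52. If 40 were scanned (an assumption), r = 0.30 gives 0.3095 × √37 = 1.883, and Φ(−0.077) = 47% instead of 58%.

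**Which added model works.** If D13 = a + bM + cD3, then D13 − D3 = a + bM + (c − 1)D3. The coefficient b is identical, so regressing the later change on M and D3 is the same test. Adjusting the later change for the week-3 score alone is not the same test, because baseline stays uncontrolled. In simulations with between-visit correlation 0.6–0.8 and r1 of 0.3–0.5, that version still flagged the marker in about 11–32% of trials at n = 52.

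**The case against.** The strongest reply is that the plan asks a plainer question. It asks whether neural change at two weeks predicts efficacy at treatment completion, and efficacy is measured from baseline. A week-3 marker that correlates with week-13 change does predict it in the ordinary sense. This stands. The percentages in the table are therefore power to detect a real correlation of 0.15–0.40. A reader might take them as false-positive rates for the planned test, but they are not. They are misleading only for the narrower claim that improvement after the scan is predicted.

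A second reply is that adding week-3 change may over-adjust. A genuine marker may act by raising cognition early, with the gain then persisting. That model implies the same correlations as a mere mirror of week-3 cognition, so the added model would pass it only about 5% of the time. This also stands. It is a reason to keep the planned regression and not to treat a null second model as evidence against the marker.

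A reader might also infer that such a marker is bound to be declared predictive. The documents do not support that: at the lower assumed correlations the chance is 16–21% at n = 52. Nor do they say that the marker must change before cognition improves or must outperform a cognitive test; the Background even names early cognitive improvement as something the signal may reflect. Finally, the aim is exploratory and the text speaks of potential predictive value.

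What these replies do not remove is the repeated word subsequent, together with a named covariate set that cannot isolate it.

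**Conclusion.** The point holds in a limited form. Cognition and neural activity are re-measured at the same week-3 assessment, the outcome at treatment completion includes the change up to that assessment, and the regression meant to show predictive value leaves that change out. A marker that only tracks concurrent cognition can then be reported as predicting later improvement, in roughly 16–81% of trials at n = 52 and 30–99% at n = 104 if the sub-studies are pooled.

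These ranges rest on assumed correlations, on everyone being scanned, and on covariates unrelated to cognition. They are lower if fewer are scanned. This is not something merely left to an analysis plan, because the article names the adjustment set. The consequence is confined to an exploratory aim: the planned regression is valid as a test of overall association with 12-week efficacy, and the primary comparison is unaffected. It is an inexpensive improvement that should be made.

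**What to change.** - Keep the planned week-13 regression and label it as the test of overall association between early neural change and 12-week efficacy.
- Add a second model with the same covariates plus the baseline-to-week-3 change in the primary composite. Modelling week-3-to-week-13 change with that same covariate is equivalent; adjusting for the week-3 score alone is not.
- Claim prediction of improvement after week 3, or value beyond the week-3 cognitive test, only from the second model.
- Describe the week-3 correlation as concurrent.
- State in advance that a null second model does not rule out a marker whose effect runs through early cognitive gain.

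The cost is one degree of freedom and a stricter, lower-powered test in an exploratory analysis. The covariate is already collected, so no extra visit or measurement is needed.

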## Background

Cognitive deficits occur in moderate to severe degree in patients with bipolar disorder (BD) and unipolar disorder (UD) [1–6]. These deficits are not only present during acute episodes, but commonly persist after remission [1–7]. This negatively affects patients’ quality of life, recovery rates, and socio-occupational functioning [6, 8–12] of which reduced work capacity is the largest area of socioeconomic burden [13, 14]. A higher occurrence of mild to moderate deficits has also been detected in BD, UD, and schizophrenia patients’ unaffected first-degree relatives compared with healthy controls with no first-degree family history of psychiatric disorder [15–19]. These impairments increase the risk of psychiatric illness onset in these individuals [20]. Cognition is therefore a key treatment priority in patients with mood disorders and genetically predisposed individuals [21]. Nevertheless, there are no existing treatments with solid and enduring efficacy on cognitive dysfunction in these populations. New candidate treatments have only produced disappointing or preliminary results [22]. This is partially related to major methodological challenges, including the absence of a sensitive brain-based biomarker model to detect the efficacy of candidate treatments in phase 1 and 2 clinical trials [23]. In fact, candidate drug treatment screening typically relies on animal models with compounds being directly moved into large-scale, costly clinical efficacy trials, in cases of beneficial effects in the animal model. However, detection of pro-cognitive efficacy in animal models has poor predictive value in clinical trials [24], which underlines the need for a more valid, sensitive biomarker model for pro-cognitive efficacy. Emerging evidence highlights blood-oxygen-level dependent (BOLD) functional magnetic resonance imaging (fMRI) response in the prefrontal cortex (PFC) as a promising biomarker for cognitive dysfunction and early cognitive improvement. In particular, aberrant (primarily hypo-) activity in the dorsolateral and medial PFC (dlPFC and mPFC) during working memory and episodic encoding tasks is the most reproducible neural marker of cognitive dysfunction across neuropsychiatric disorders, including BD, UD, schizophrenia, and genetically predisposed individuals [25–31]. This aberrant activity reflects difficulties with selecting and maintaining stimuli in working memory and strategic memory encoding [32]. Reversal of aberrant dorsal prefrontal activity may therefore constitute a promising neural biomarker for cognitive improvement.

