
Preclinical and clinical studies point to erythropoietin (EPO) as one of the most promising candidate cognitive enhancement treatments [33]. EPO is produced in the brain where it exerts neurotrophic and neuroprotective actions and plays a central role in cognitive functioning [33–37]. Clinical studies have found that repeated systematically administered high-dose recombinant human EPO versus placebo (saline) improves attention, memory, and executive functions after 8–12 weeks of treatment across neuropsychiatric disorders, including multiple sclerosis, Parkinson’s disease, schizophrenia, treatment-resistant depression (TRD; defined as failure to respond to ≥ 2 different types of antidepressant treatments given in sufficient doses over sufficient time [38]), and BD [39–43]. In particular, two randomized placebo-controlled trials from our group revealed that eight weekly EPO infusions improved several cognitive domains in patients with BD and TRD [39, 40]. This was accompanied by increased activity in dlPFC and dorsomedial PFC (dmPFC) during working memory and episodic encoding tasks [44, 45]. Notably, a single dose of EPO enhances cognition-related dlPFC and dmPFC activity without producing any change in red blood cells [46, 47]. This suggests that the EPO-associated increase in task-related dorsal PFC (dPFC) reflects direct effects of EPO in the brain. Taken together, these preliminary findings point to EPO as a promising cognition treatment and to neuronal activity change in the dPFC as a key neural correlate of treatment-related improvement of cognition. Nevertheless, our EPO trial had a number of methodological limitations [39, 40]. First, cognitive dysfunction was not verified with an objective (i.e. neuropsychological) measure before enrollment of participants. This is problematic since we found in post-hoc analyses that objective cognitive impairment at baseline was the strongest predictor of treatment success on cognition [48, 49]. Second, the primary outcome was a single measure of verbal memory, which contrasts with the recently published recommendations by the International Society for Bipolar Disorders (ISBD) Targeting Cognition Task Force that the primary outcome in cognition trials should be a broad cognitive composite score spanning attention, memory, and executive function [50]. Third, the lack of long-term follow-up assessment hampered insight into whether treatment-associated cognitive improvement was long-lasting. Fourth, we had not assessed functional capacity in the patient sample and thus had no insight into whether the EPO-related improvement of cognition translated into better functional capacity.

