### Exploratory measures of potential pro-cognitive effects

To further increase insight into the underlying neurobiological mechanisms involved in the potential beneficial cognitive effects of EPO, blood samples from baseline, week 3, and after treatment will be analyzed for the exploratory purpose of investigating whether baseline levels and/or changes of peripheral biomarkers, including inflammatory markers, brain-derived neurotrophic factor (BDNF), and metabolic parameters (fat and glucose markers), are correlated with cognitive improvement [76–83]. Baseline blood samples will also be used for assessment of potential influence of Catechol-O-methyltransferase (COMT: Val158Met), BDNF: Val66Met, and EPO and EPO-R genotypes on the treatment-related change in cognition and neural activity.

We will perform post-hoc exploratory analyses investigating which demographic, clinical, cognitive, and neural variables at baseline predict treatment efficacy on the primary cognitive outcome measure, since there is a paucity of research into which baseline factors are associated with cognitive improvements [84].

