#### Sample size and power calculation

Sample size and statistical power has been calculated by PharmaConsulting Group AB with Statistical Analysis Software (SAS), based on our previous findings assessing cognitive effects of weekly infused EPO [48]. The difference in cognitive change between the EPO and the saline-treated groups from baseline to after treatment was 0.5 SD [48]. In this trial, we estimate a clinically relevant differential change in the primary cognitive composite score between the EPO and placebo groups from baseline to week 13 (treatment completion) to be at least 0.4 SD (corresponding to a moderate effect size) with a SD of the mean change of 0.5 between these groups. This is consistent with the recommendations listed by the ISBD Cognition Task Force [50]. Specifically, the task force indicated that a differential change between groups of 0.2–0.4 SD on a global composite score reflects a potentially clinically relevant change, since this may translate into moderate–large functional improvement in patients with mood disorders [50]. In our eight-week EPO trial, the difference regarding change in the cognitive composite score from baseline to treatment completion was 0.5 SD between the EPO and the saline groups [48]. Based on the ISBD task force recommendations and our earlier findings regarding effects of longer-term EPO treatment, we estimate that a sample size of *N* = 104 (i.e. *n* = 52 participants within each sub-study with *n* = 26 in each treatment group) will reach a ≥ 80% power for detecting a similar clinically relevant differential change of 0.4 SD in the primary cognitive composite outcome measure with a SD of this change of 0.5 between the treatment groups at an alpha level of 5% (two-sided test). Based on our assumption of a 10% drop-out rate from baseline to treatment completion, we plan to recruit up to *n* = 58 for each sub-study to achieve complete datasets for *n* = 52 participants per sub-study (first-degree relatives and patients, respectively).

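### The regression testing whether early neural change predicts cognitive gain omits baseline cognition, so a significant neural term could partly reflect baseline impairment

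*Protocol article*

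**What the plan says.** The section Functional MRI analyses sets out two steps. First, "Differences in neural activity between groups will be correlated with potential change in the primary cognitive composite score at week 3 and after treatment completion". When this first step reaches the 5% level, a second follows: "multiple regression analyses will be performed with adjustment for mood symptoms, age, and gender to assess the potential predictive value". The value in question is that of the week-3 neural signal for efficacy after 12 weeks. The same section adjusts week-3 activity for baseline activity when the EPO and saline groups are compared. Nowhere does it adjust for baseline cognition.

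The Background supplies the other two elements. In post-hoc analyses of the group's earlier trial, "objective cognitive impairment at baseline was the strongest predictor of treatment success on cognition". Aberrant, mainly reduced, dorsal prefrontal activity during memory tasks "is the most reproducible neural marker of cognitive dysfunction across neuropsychiatric disorders".

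Under Exploratory measures of potential pro-cognitive effects, a separate post-hoc analysis will ask "which demographic, clinical, cognitive, and neural variables at baseline predict treatment efficacy on the primary cognitive outcome measure". It is not said to feed into the fMRI regression. Aims and hypotheses presents the fMRI aim as exploratory: "Third, we will explore with fMRI the early neuronal changes that are predictive of subsequent clinically relevant cognitive improvement across these groups".

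**The concern.** By the protocol's own account, baseline impairment is tied to both sides of this regression. Participants with lower baseline cognition tend to gain more, through regression to the mean, through response, or both. The same participants tend to have aberrant prefrontal activity, which may itself move on retest or persist at week 3. If baseline cognition is left out, the neural term can pick up this shared dependence. The preceding correlation does not screen it out, because it is open to the same confounding.

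What is at stake is the interpretation of the biomarker aim. The Perspectives section would present prefrontal target engagement as a promising biomarker model if early change is associated with efficacy. That reading is more secure if the association does not run through a baseline score that is already collected.

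**Working it through.** **The plan's own figure.** The protocol states no figure for this regression. Its power statement concerns the primary composite: difference 0.4, SD of change 0.5, two-sided 5%. Required n per arm = 2 × (1.96 + 0.84)² × (0.5/0.4)² ≈ 24.5, so 25. With 26 per arm the power is 82.2% (80.7% by exact t). Allowing for 10% drop-out, 52/0.9 = 57.8, so 58. These figures reproduce and are not in dispute.

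**Inputs**
- From the protocol: SD of change 0.5; 52 participants per sub-study; two-sided 5%; covariates mood symptoms, age and gender.
- Assumed, because the protocol gives none: correlation ρ between baseline activity and baseline composite of 0.3 to 0.6; retest correlation of activity 0.5; size g of the negative correlation between baseline composite and cognitive gain of 0.25 to 0.6.
- The lower value of g has an anchor. If the composite has SD 1 at both visits (assumption), the retest correlation is 1 − 0.5²/2 = 0.875, and corr(baseline, change) = −(1 − 0.875)/0.5 = −0.25.

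**Set-up.** Neural change has no direct link with cognitive change. Any correlation between them is then the product of corr(neural measure, baseline composite) and corr(baseline composite, gain).

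*Structure A: week-3 activity depends on baseline cognition only through measured baseline activity (A3 = 0.5·A0 + noise).*
- Raw difference A3 − A0: covariance with the baseline composite is −0.5ρ and the variance is 2(1 − 0.5) = 1, so the correlation is −0.5ρ. The induced correlation with gain is 0.5ρg.
- A3 adjusted for A0: no remaining link, so no inflation.

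*Structure B: both scans are noisy measures of one stable trait, each with reliability 0.5.*
- Raw difference: covariance with the baseline composite is ρ − ρ = 0, so no inflation.
- A3 adjusted for A0: the residual A3 − 0.5·A0 has covariance 0.5ρ with the baseline composite and variance 0.75, so the correlation is 0.5ρ/√0.75 = 0.577ρ. The induced correlation with gain has size 0.577ρg, with negative sign.

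For an induced correlation r, the approximate rejection rate is Φ(−1.96 + δ) + Φ(−1.96 − δ), with δ = r√52/√(1 − r²).

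| ρ, g | A, raw difference: r | Approx. rate | Simulated rate | B, adjusted for baseline activity: size of r | Approx. rate |
|---|---|---|---|---|---|
| 0.3, 0.25 | 0.038 | 6% | 6.1% | 0.043 | 6% |
| 0.3, 0.5 | 0.075 | 8% | 8.6% | 0.087 | 10% |
| 0.5, 0.5 | 0.125 | 15% | 14.5% | 0.144 | 18% |
| 0.6, 0.6 | 0.180 | 26% | 23.7% | 0.208 | 33% |

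Simulation of structure B gives about 6–33% over the same settings. With the baseline composite added, the simulated rate is about 5% in every setting of both structures.

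Each way of forming the neural predictor is therefore safe in one structure and not in the other. Including baseline cognition is safe in both.

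**The case against.** The strongest objection is that the protocol does adjust week-3 activity for baseline activity, so a calculation on a raw difference may describe an analysis that is not planned. This largely stands. Under structure A the stated adjustment removes the inflation completely. It does not settle the matter, for two reasons. The regression sentence speaks only of early neural activity change and does not say how the adjustment carries over. And if baseline activity is measured with error, the adjusted measure keeps a link with baseline cognition. In that case the spurious coefficient is mostly negative, the opposite of what recovery from under-activity would suggest. A two-sided test would still count it, but a careful reader might not take it as support.

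Other limits also stand. The protocol gives no correlation between activity and cognition. Enrolling only participants who are impaired on the screening test may narrow the baseline range and weaken the confounding. The Background refers to objective impairment, not literally to the composite. Added value over a baseline score is a stricter question than the one the protocol sets itself.

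A reader might infer that the two sub-studies are pooled without a sub-study term. At n = 104 the ranges would be about 7–45% (structure A, raw difference) and 7–61% (structure B, adjusted). The document does not support this inference: the phrase about these groups belongs to the aims, no pooled regression is stated, and each sub-study is randomised and powered separately.

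Nor is this simply detail left to an analysis plan. The article states a covariate list, and that list lacks the predictor that the article itself ranks first.

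**Conclusion.** The point holds as a conditional weakness of an exploratory analysis. The stated covariates omit baseline cognition, and the protocol's own Background gives reason to expect it to be related to both neural activity and cognitive gain.

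The size is uncertain. With no true neural prediction and n = 52, the false-positive rate runs from about 5% to about 24% (raw change score, structure A) or about 33% (baseline-adjusted activity, structure B). The upper values need ρ and g both at 0.6, which nothing in the document establishes. At g = 0.25, the one value linked to a protocol figure, with ρ = 0.3, the rate is only about 5–6%.

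It would go too far to say that an uninformative scan is likely to be declared predictive, or that the trial's efficacy conclusions are at risk. The first depends on unreported correlations. The second does not follow, because the randomised comparison of the primary composite does not use this regression.

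**What to change.** Regress the week-13 composite on week-3 activity, with baseline activity and the baseline composite added to mood symptoms, age and gender. Add sub-study only if the two are analysed together. Base the exploratory statement on predictive value on the neural term in that model. Once the baseline composite is a covariate, using the week-13 score or the change score as outcome gives the same neural coefficient.

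The cost is one or two degrees of freedom. The baseline composite and baseline scan are already collected, and the primary efficacy analysis does not change.
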